# Evaluating the impact of 18F-FDG-PET-CT on risk stratification and treatment adaptation for patients with muscle-invasive bladder cancer (EFFORT-MIBC): a phase II prospective trial

**DOI:** 10.1186/s12885-021-08861-x

**Published:** 2021-10-18

**Keywords:** Muscle-invasive bladder cancer, Primary staging, ^18^F-FDG-PET-CT, Distant metastasis, Oligometastasis, Neo-adjuvant chemotherapy, Metastasis-directed therapy, Stereotactic body radiation therapy, Immunotherapy, Overall survival

## Abstract

**Background:**

The outcome of patients with muscle-invasive bladder cancer (MIBC) remains poor, despite aggressive treatments. Inadequate primary staging, classically performed by computed tomography (CT)-imaging, could lead to inappropriate treatment and might contribute to these poor results. Although not (yet) adapted by international guidelines, several reports have indicated the superiority of ^18^F-fluorodeoxyglucose-positron emission tomography-CT (^18^F-FDG-PET-CT) compared to CT in the detection of lymph node and distant metastases. Thereby the presence of extra-vesical disease on ^18^F-FDG-PET-CT has been correlated with a worse overall survival. This supports the hypothesis that ^18^F-FDG-PET-CT is useful in stratifying MIBC patients and that adapting the treatment plan accordingly might result in improved outcome.

**Methods:**

EFFORT-MIBC is a multicentric prospective phase II trial aiming to include 156 patients. Eligible patients are patients with histopathology-proven MIBC or ≥ T3 on conventional imaging treated with MIBC radical treatment, without extra-pelvic metastases on conventional imaging (thoracic CT and abdominopelvic CT/ magnetic resonance imaging (MRI)). All patients will undergo radical local therapy and if eligible neo-adjuvant chemotherapy. An ^18^F-FDG-PET-CT will be performed in addition to and at the timing of the conventional imaging. In case of presence of extra-pelvic metastasis on ^18^F-FDG-PET-CT, appropriate intensification of treatment with metastasis-directed therapy (MDT) (in case of ≤3 metastases) or systemic immunotherapy (> 3 metastases) will be provided. The primary outcome is the 2-year overall survival rate. Secondary endpoints are progression-free survival, distant metastasis-free survival, disease-specific survival and quality of life. Furthermore, the added diagnostic value of ^18^F-FDG-PET-CT compared to conventional imaging will be evaluated and biomarkers in tumor specimen, urine and blood will be correlated with primary and secondary endpoints.

**Discussion:**

This is a prospective phase II trial evaluating the impact of ^18^F-FDG-PET-CT in stratifying patients with primary MIBC and tailoring the treatment accordingly. We hypothesize that the information on the pelvic nodes can be used to guide local treatment and that the presence of extra-pelvic metastases enables MDT or necessitates the early initiation of immunotherapy leading to an improved outcome.

**Trial registration:**

The Ethics Committee of the Ghent University Hospital (BC-07456) approved this study on 11/5/2020. The trial was registered on ClinicalTrials.gov (NCT04724928) on 21/1/2021.

**Supplementary Information:**

The online version contains supplementary material available at 10.1186/s12885-021-08861-x.

## Background

Bladder cancer is the 10th most frequently diagnosed cancer and ranks 14th in causes of cancer-related death worldwide [1]. As the incidence of bladder cancer increases steadily with age and life expectancy improves, the number of bladder cancer patients of whom approximately 30% are diagnosed with muscle-invasive bladder cancer (MIBC) [2], is expected to increase in the future [3]. Despite an aggressive treatment with neo-adjuvant chemotherapy [4] followed by either radical cystectomy (RC) or trimodality therapy (TMT) [5], the outcome of MIBC patients remains poor with 2- to 5-year overall survival (OS) rates of ±60 and 50%, respectively [3, 4] and a 2-year disease free survival rate of ±64% [3]. Inadequate primary staging probably contributes to these poor results as adequate staging and appropriate treatment are closely linked.

Staging is classically done by computed tomography (CT) of the chest, abdomen and pelvis [6]. Although several reports indicate the superiority of ^18^F-fluorodeoxyglucose-positron emission tomography-CT (^18^F-FDG-PET-CT) compared to CT in the detection of lymph node as well as distant metastases [7], ^18^F-FDG-PET-CT is currently not recommended in international guidelines [6].

The presence of metastases on ^18^F-FDG-PET-CT has been correlated with survival rates. When compared to patients without metastatic lesions on ^18^F-FDG-PET-CT, MIBC patients with metastases on ^18^F-FDG-PET-CT had inferior OS and disease-specific survival (DSS). At 2 years the difference increased to 35% for both OS and DSS in favor of ^18^F-FDG-PET-CT-negative MIBC patients [8]. This suggests that there is a role for ^18^F-FDG-PET-CT in risk stratification to guide optimal treatment strategy.

For patients with metastatic disease on ^18^F-FDG-PET-CT, we hypothesize that treatment intensification improves outcome. In analogy with other tumor types [9–11], trials -although limited in patient number- have demonstrated that metastasis-directed therapy (MDT) of a limited number of metastases results in improved and durable disease control [12]. Similarly, patients with multiple metastases on ^18^F-FDG-PET-CT can benefit from earlier initiation of systemic immunotherapy [13].

To our knowledge, there is currently no prospective trial evaluating the impact of ^18^F-FDG-PET-CT implementation in the staging of patients with MIBC, to stratify patients and guide further treatment decisions in order to improve the outcome of patients with primary MIBC.

## Methods/design

This study is approved by the Ethics Committee of the Ghent University Hospital (BC-07456) and the Belgian Federal Agency for Nuclear Control (PK-0061377). The trial is registered on ClinicalTrials.gov (NCT04724928).

In this multicentric prospective phase II trial, patients with MIBC will be offered ^18^F-FDG-PET-CT in addition to and at the timing of the conventional imaging (thoracic CT and abdominopelvic CT/ magnetic resonance imaging (MRI)), to guide further treatment after radical local therapy. In case of presence of metastasis on ^18^F-FDG-PET-CT, appropriate intensification of treatment with MDT or immunotherapy will be provided. A flowchart presenting the different steps from inclusion until follow-up (as described below) is presented in Fig. 1. Items from the World Health Organization Trial Registration Data Set are addressed in an additional file (see additional file 1).

**Fig. 1 Fig1:**
[figure not shown]
Overview of the EFFORT-MIBC study design. (1) Inclusion and exclusion criteria need to be fulfilled to be included in the study. (2) Stratification into treatment arms is based on the ^18^F-FDG-PET-CT result. In case of neo-adjuvant chemotherapy, stratification is based on the results of both ^18^F-FDG-PET-CT’s (e.g. prior to and after neo-adjuvant chemotherapy). Abbreviations: MIBC: muscle-invasive bladder cancer; CT: computed tomography; MRI: magnetic resonance imaging; ^18^F-FDG-PET-CT: ^18^F-fluorodeoxyglucose-positron emission tomography-computed tomography; MDT: metastasis-directed therapy

### Objectives

The primary endpoint is the 2-year overall survival (OS) rate defined as the percentage of patients alive at 2 years after diagnosis of MIBC. OS is calculated from time of diagnosis until death due to MIBC or other causes.

Secondary endpoints are progression-free survival (PFS, defined as time of diagnosis until progression: i.e. local (T2-T4 in case of of TMT)/locoregional recurrence or extra-pelvic metastases), distant metastasis-free survival (DMFS, defined as time of diagnosis until occurrence of distant metastasis on repeated imaging), disease-specific survival (DSS, defined as time of diagnosis until death due to MIBC) and quality of life (QOL) evaluated by the general EORTC QOL questionnaire QLQ-C30 (version 3) and the bladder cancer specific module QLQ-BLM30. The added diagnostic value of ^18^F-FDG-PET-CT compared to conventional imaging will be evaluated. If neo-adjuvant chemotherapy is administered, the treatment response will be evaluated on the repeated ^18^F-FDG-PET-CT. A biopsy specimen of the bladder, obtained after transurethral resection of the bladder (TURb) as well as urine and blood samples will be collected for validation of predictive biomarkers by evaluating the correlation between response to therapy and outcome (PFS, DMFS, DSS and OS) with in literature reported biomarkers determined on biopsy specimen of the bladder, obtained after TURb.

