### Follow up and data collection

An overview of the different follow-up moments and associated assessments and investigations is presented in Fig. 2. Adverse events (AE) will be assessed using the Common Terminology Criteria for Adverse Events version (CTCAE) 5.0 [14].. Patients will be instructed by the investigator to report the occurrence of any AE. The investigator assesses and records all AE observed during the AE reporting period from inclusion until 5 years after inclusion. QOL will be assessed using the European Organisation for Research and Treatment of Cancer (EORTC) QLQ-C30 [15] and QLQ-BLM30 [16] questionnaires. Imaging studies are done conform standard of care. In case of TMT a routine cystoscopy is advocated every 3 months during the first year of follow-up and 6-monthly thereafter until 5 years. Patients will be followed up until death or disease progression defined as per: Response Evaluation Criteria in Solid Tumors (RECIST)-criteria [17]. Once disease progression has been confirmed, survival status will be assessed 3-monthly until death, withdrawal of consent or the end of the study, whichever occurs first. Patients who are no longer followed in the center of inclusion or who refuse follow-up visits but are willing to have telephone follow-up will be contacted by phone at the scheduled follow-up time points.

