#### Subsequent analyses

Descriptive statistics will be used to summarize patient characteristics and toxicity per treatment group. Progression and survival are defined as mentioned above and calculated from time of diagnosis to disease progression or death. Survival analysis will be compared between groups using the log-rank test. Kaplan-Meier estimates of 2-year PFS, DMFS, DSS and OS will be provided for each treatment group and as a post-hoc subgroup analysis based on patient characteristics described above. Median follow-up time will be derived using both complete and incomplete follow-up times. Cox proportional hazards regression will be used to provide hazard ratio estimates. A *p*-value of less than 0.05 will be considered statistically significant. For the evaluation of biomarkers on one time point, differences between groups will be tested using the Mann-Whitney U test. For the evaluation of biomarkers over time, differences between groups will be tested using the Wilcoxon signed-rank test. To evaluate correlations, Spearman correlation coefficients will be calculated. A p-value of less than 0.05 will be considered statistically significant.

All statistical analyses will be performed using SPSS (SPSS Inc., Chicago, Il, USA).

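### PFS and DMFS are defined without death as an event, and the analysis section leaves it unclear whether death counts for PFS

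*Protocol article*

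**What the plan says.** All passages are in the protocol article.

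- **Objectives, PFS:** "progression-free survival (PFS, defined as time of diagnosis until progression", followed by the events that count: local recurrence (T2–T4 after TMT), locoregional recurrence or extra-pelvic metastases. Death is not listed.
- **Objectives, DMFS:** "DMFS, defined as time of diagnosis until occurrence of distant metastasis on repeated imaging". Death is not listed.
- **Objectives, DSS and OS, for contrast:** "DSS, defined as time of diagnosis until death due to MIBC", and "OS is calculated from time of diagnosis until death due to MIBC or other causes". Death is named where it is meant to count.
- **Subsequent analyses:** progression and survival follow the definitions given before and are "calculated from time of diagnosis to disease progression or death". The section then plans 2-year Kaplan-Meier estimates of PFS, DMFS, DSS and OS for each treatment group, log-rank comparisons and Cox hazard ratios. It does not say how a death before progression or metastasis is handled.
- **Follow up and data collection:** "Patients will be followed up until death or disease progression defined as per: Response Evaluation Criteria in Solid Tumors (RECIST)-criteria". After confirmed progression, only survival status is collected.

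**The concern.** PFS and DMFS are usually read as the chance of being alive and free of the event. As the Objectives section defines them, they are time to progression and time to metastasis. A patient who dies with no documented recurrence has no PFS event. A patient who dies, even of bladder cancer, with no metastasis on imaging has no DMFS event. A standard Kaplan-Meier analysis of these definitions censors such patients at death, as though they could still have progressed later.

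Two things are at stake. First, the 2-year figures would lie above the event-free survival that their names imply. The gap would be largest in a group with many deaths before documented progression, which matters because the trial compares groups. Second, two analysts could read the sentence in Subsequent analyses differently and draw different PFS curves from the same data.

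**Working it through.** **1. The plan's own figures.** The protocol article states no expected value for PFS, DMFS or DSS. Its only sample-size figure concerns 2-year OS in arms 2 and 3 together, and that figure reproduces. With 38% against 63%, an exact binomial test and 35 patients, the rule of 20 or more survivors has an upper-tail probability of 0.0167 under 38% and power 0.815 under 63%. That fits a two-sided 5% level. Then 35/0.90 = 38.9, rounded up to 39, and 39/0.25 = 156. None of this depends on how PFS or DMFS is defined.

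**2. The passages side by side.**

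| Place | PFS event | DMFS event | Death counted? |
|---|---|---|---|
| Objectives | Recurrence or extra-pelvic metastases | Distant metastasis on imaging | No |
| Subsequent analyses, composite reading | Progression or death | Not addressed | Yes, for PFS only |
| Subsequent analyses, read as *respectively* | Progression | Not addressed | No |

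On the composite reading the two sections contradict each other for PFS. On the other reading they agree, and death is left out. On either reading DMFS stays without death.

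**3. Size for PFS and DMFS.** Inputs:

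- Illustrative 2-year composite (progression or death) S = 0.64. This borrows the level of the background 2-year disease-free survival of about 64%. How that figure treated deaths is not stated, so it serves only as a plausible level.
- Share s of first events that are deaths: 5%, 10%, 20%, 30%. This is assumed; the document gives no figure.
- Constant cause-specific hazards (assumed).

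Formulas, with H = −ln(S):

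- Composite event-free survival: exp(−H) = S
- Kaplan-Meier with deaths censored: exp(−H(1 − s)) = S^(1 − s)
- One minus cumulative incidence of progression: 1 − (1 − s)(1 − S)

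For S = 0.64, H = 0.446. For s = 0.10, Kaplan-Meier = 0.64^0.90 = 0.669.

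| s | Composite | Kaplan-Meier, deaths censored | Excess (points) | 1 − cumulative incidence |
|---|---|---|---|---|
| 5% | 64.0% | 65.4% | 1.4 | 65.8% |
| 10% | 64.0% | 66.9% | 2.9 | 67.6% |
| 20% | 64.0% | 70.0% | 6.0 | 71.2% |
| 30% | 64.0% | 73.2% | 9.2 | 74.8% |

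At a composite of 50%, Kaplan-Meier runs from 51.8% (s = 5%) to 61.6% (s = 30%), an excess of 1.8 to 11.6 points.

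**4. The same check for DSS.** Here the event is death from MIBC and s is the assumed share of deaths from other causes. With 2-year OS of 60%, the background figure:

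| s | Kaplan-Meier, other deaths censored: 0.60^(1 − s) | 1 − cumulative incidence: 1 − (1 − s)(0.40) | Difference (points) |
|---|---|---|---|
| 10% | 63.1% | 64.0% | −0.9 |
| 20% | 66.5% | 68.0% | −1.5 |
| 30% | 69.9% | 72.0% | −2.1 |

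Kaplan-Meier is lower here. With OS at 38% it is 2.3 to 5.8 points lower over the same shares.

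**The case against.** The strongest reply is that no passage says deaths will be censored. The analysis section mentions death, so on its composite reading deaths count for PFS and the overstatement there disappears. The article is condensed, and an analysis plan that is not shown may set the censoring rules. This stands in part: overstatement is conditional on following the Objectives section. It does not remove the point. The Objectives definitions are stated in full, and an analysis plan would have to override them to count death. The composite reading also does nothing for DMFS.

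A second reply is that overstatement needs a target. Measured against the literal definitions, Kaplan-Meier lies below one minus cumulative incidence (66.9% against 67.6% at s = 10%). That is correct. The overstatement is relative to event-free survival with death included, which is what the survival names imply.

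Three stronger readings are tempting and are not supported:

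- **That DSS is overstated too.** A reader might infer this because DSS also goes into Kaplan-Meier with other deaths censored. But DSS excludes other-cause deaths by design, which is conventional, and against cumulative incidence the difference runs the other way.
- **That the RECIST sentence is a third PFS definition.** It governs when regular follow-up ends and does not mention PFS. RECIST may simply be how the listed events are assessed. What is missing is a statement of how the two relate.
- **That the main result is at risk.** OS counts death from any cause, so the primary endpoint is untouched.

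**Conclusion.** The point holds for PFS and DMFS. Both are defined without death under survival names, and the analysis section is ambiguous on whether death counts for PFS. If the Objectives definitions are used, the 2-year Kaplan-Meier figures would exceed event-free survival by about 1.4 to 9.2 points at a 64% composite. That range rests on assumed death shares of 5% to 30% of first events and on constant hazards; the document gives neither. Only secondary endpoints are affected, but the correction is cheap and should be made before analysis.

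**What to change.** 1. Define PFS as time from diagnosis to the first of local recurrence (T2–T4 after TMT), locoregional recurrence, extra-pelvic metastasis or death from any cause. Define DMFS as time from diagnosis to distant metastasis or death from any cause.
2. If death is deliberately left out, rename the endpoints time to progression and time to metastasis, and report cumulative incidence with death as a competing event.
3. Reword the sentence in Subsequent analyses so that it names the event for each endpoint and agrees with Objectives.
4. State how the RECIST criterion in Follow up and data collection relates to the event list in Objectives.

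DSS, OS and the sample size need no change on this account. The cost is wording, since deaths are already collected for OS. Under option 1 the reported PFS and DMFS would be somewhat lower than with deaths censored.

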### Intervention

#### Imaging

Conventional imaging, consisting of standard thoracic CT and abdominopelvic CT (or MRI), will be performed prior to the radical local therapy. In case of neo-adjuvant chemotherapy, conventional imaging will be performed prior to and after neo-adjuvant chemotherapy. After the second cycle of chemotherapy, MRI bladder will be performed to evaluate provisional therapy response. In addition to and at timing of the conventional imaging patients will receive an ^18^F-FDG-PET-CT. We aim to perform the ^18^F-FDG-PET-CT within 1 month of the thoracic CT and abdominopelvic CT (or MRI).

The ^18^F-FDG-PET-CT procedure is described in detail in an additional file (see Additional file 2).

Conventional imaging images will be evaluated by experienced radiologists in uro-oncology. ^18^F-FDG-PET-CT images will be reviewed and analyzed by a nuclear medicine physician and a radiologist experienced in reading PET-CT images. Evaluation of the ^18^F-FDG-PET-CT images will occur blinded to the conventional imaging or vice versa in case the ^18^F-FDG-PET-CT is performed first.

After ruling out presence of distant metastases on conventional imaging and evaluation of the ^18^F-FDG-PET-CT’s, patients will be allocated to the appropriate treatment arm:
Arm 1: ^18^F-FDG-PET-CT ➜ T1–4 N0–3 M0Arm 2: ^18^F-FDG-PET-CT ➜ T1–4 N0–3 M1 (≤3 metastases)Arm 3: ^18^F-FDG-PET-CT ➜ T1–4 N0–3 M1 (> 3 metastases)

If no neo-adjuvant chemotherapy is administered, group allocation is based on the findings of the single ^18^F-FDG-PET-CT. In case of neo-adjuvant chemotherapy, group allocation is based on ^18^F-FDG-PET-CT with the highest number of distant metastases. Thus, patients who show a decrease of the total number of metastases or a complete response on the second ^18^F-FDG-PET-CT, will be allocated based on the result of their first ^18^F-FDG-PET-CT.

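### DMFS, and less clearly PFS, do not separate new metastases from the index lesions that place patients in arms 2 and 3

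*Protocol article*

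**What the plan says.** All references are to the protocol article.

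- **Objectives.** The DMFS definition reads: "distant metastasis-free survival (DMFS, defined as time of diagnosis until occurrence of distant metastasis on repeated imaging". The PFS event is "local (T2-T4 in case of of TMT)/locoregional recurrence or extra-pelvic metastases", also timed from diagnosis. Neither definition requires the metastasis to be new or makes an exception for patients already M1.
- **Intervention, Imaging.** Arm 2 is "T1–4 N0–3 M1 (≤3 metastases" on PET and arm 3 is "T1–4 N0–3 M1 (> 3 metastases". After neo-adjuvant chemotherapy there are two PETs, and "group allocation is based on ^18^F-FDG-PET-CT with the highest number of distant metastases".
- **Subsequent analyses.** "Kaplan-Meier estimates of 2-year PFS, DMFS, DSS and OS will be provided for each treatment group". The same section says "Survival analysis will be compared between groups using the log-rank test", and refers back to the article's earlier definitions of progression and survival.
- **Follow up and data collection.** RECIST is named as the standard for the progression that ends regular follow-up. The section does not say whether it also governs the PFS endpoint.

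**The concern.** The finding that puts a patient in arm 2 or 3 is of the same kind as the event that DMFS and PFS count. Without a rule on baseline lesions, a result in these arms could reflect how many patients still showed their index lesion at the next scan, rather than how many developed further disease after treatment was intensified. These are the listed endpoints closest to disease control after MDT or immunotherapy, so the trial's hypothesis leans on them. The biomarker objective also relates markers to PFS and DMFS, and would partly be relating them to M status at staging.

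The two-PET rule adds a second problem. In patients given neo-adjuvant chemotherapy, the repeat PET can both produce a DMFS event and decide the arm. Arm membership then depends on something observed after the clock has started at diagnosis.

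**Working it through.** **Inputs.** From Sample size: 156 patients in total, 1/4 expected PET-positive, 35 evaluable patients in arms 2+3, 10% drop-out. From Objectives, Imaging and Subsequent analyses: the definitions quoted above. As the sample size itself does, I take PET-positive to mean M1 on PET.

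**1. The plan's own figures.** 35 / (1 − 0.10) = 38.9, rounded up to 39; 39 / (1/4) = 156. Both agree with the article. An exact binomial test of 38% against 63% with n = 35 and a 2.5% upper tail rejects at 20 or more survivors, with exact alpha 0.0167 and power 0.815. The stated 80% is reproduced. This calculation concerns OS only and does not depend on the DMFS or PFS definitions.

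**2. How many patients are exposed.** 156 × 1/4 = 39, or 25% of the trial. This is the number whose DMFS or PFS depends on how index lesions are treated. It is not a count of events.

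**3. How far the estimate could move.** Let f be the share of arm 2+3 patients whose index lesion is counted as an event on a repeat scan within 2 years. The article gives no value for f, so the full range is shown. Ignoring censoring, 2-year DMFS in arms 2+3 is at most 1 − f, and in the whole trial at most 1 − 0.25 × f.

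| f (assumed) | Ceiling, arms 2+3 | Ceiling, all patients |
|---|---|---|
| 0 | 100% | 100% |
| 0.5 | 50% | 87.5% |
| 1 | 0% | 75% (117/156) |

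The definition does not fix where in this range the trial would fall.

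**4. The patient who converts on the second PET.** Take a patient who is M0 on the first PET and M1 on the post-chemotherapy PET.

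- Under Objectives, a distant metastasis has occurred on repeated imaging, so DMFS has an event at that scan.
- Under Imaging, the PET with more metastases decides, so the patient is allocated to arm 2 or 3.
- The event is therefore charged to arm 2 or 3 and can never be charged to arm 1.

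Among patients given neo-adjuvant chemotherapy, arm 1 thus has no PET-detected event from diagnosis to the second PET, by construction. A log-rank test of DMFS from diagnosis would favour arm 1 over that interval for reasons unrelated to treatment or prognosis. The number of such patients cannot be derived from the article.

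**The case against.** A reader might infer that every patient in arms 2 and 3 has the event at diagnosis, so that DMFS and PFS there are about 0% whatever the treatment does. The documents do not support that.

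- The DMFS wording asks for repeated imaging, so a first PET is not itself a DMFS event.
- PFS is time to progression, and a staging finding is naturally read as baseline. Subsequent analyses refers back to earlier definitions, and the RECIST rule is among the earlier text. Criteria of that kind judge change from a baseline, so a stable or shrinking known lesion would not count.
- All enrolled patients are M0 on conventional imaging, so index lesions in arms 2 and 3 were visible only on PET. Follow-up imaging follows usual care, and the article's Background describes staging as classically CT-based. Some index lesions may never show on follow-up scans. The follow-up schedule figure is not available to settle this.
- The allocation rule itself foresees metastases disappearing by the second PET, and arm 2 lesions may be resected or irradiated before the next scan.
- The log-rank sentence does not name PFS or DMFS; only the Kaplan-Meier sentence does.
- Detailed event rules are often left to the full protocol or SAP, which are not shown.

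Most of this stands, and it limits the size of the problem. It does not remove it. A persisting lesion on a repeat scan still meets the DMFS wording, and so does a lesion first seen on the second PET. RECIST is attached to the duration of follow-up, while Objectives gives PFS its own explicit list of events, so the two must be reconciled. Nor is the point a mere omission: the article states both the definitions and their use in each arm, and as stated they do not fit together.

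**Conclusion.** The point holds for DMFS and, less clearly, for PFS. Neither endpoint separates new from index lesions, although arms 2 and 3 are M1 on PET by definition. About 39 of 156 patients are exposed, on the article's assumption that 1/4 are PET-positive. Under the literal wording, baseline status would lower 2-year DMFS in arms 2 and 3 by an amount that the document does not determine; 0% is reached only if every index lesion is counted on a repeat scan. Separately, allocation by the second PET keeps arm 1 free of PET-detected events up to that scan among patients given neo-adjuvant chemotherapy, which biases any arm 1 comparison timed from diagnosis. Both endpoints are secondary, and the primary 2-year OS and its sample size are untouched.

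**What to change.** 1. In all arms, define the DMFS event, and the metastatic part of the PFS event, as a new extra-pelvic lesion not present on the allocating PET or unequivocal progression of a known lesion.
2. Reconcile the PFS definition in Objectives with the RECIST progression in Follow up and data collection, and state which one governs the endpoint.
3. For any between-group comparison of PFS or DMFS, use one time origin for all arms, at or after completion of the allocating imaging (a landmark). A separate origin for arms 2 and 3 alone is not needed and would make the arms harder to compare.
4. If no landmark is adopted, report PFS and DMFS descriptively by arm, without a log-rank test of arm 1 against arms 2 and 3.

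The cost is wording plus slightly shorter event times under the landmark, or the loss of one secondary comparison. No additional patients are needed. The wording should be fixed before outcomes are analysed, because a definition chosen afterwards would be open to challenge.
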